**Fig. 2 Fig2:**

Study flow

RAND will contact the patient and describe the study in more detail. A RAND study team member will meet patients in person at the clinic, however, if in-person contact is not feasible, this procedure could occur by phone. RAND staff will ask patients for permission to contact their SP. The goal would be to identify SPs who have a significant impact on their life [50]. RAND will recruit the patient at their first or second visit with the medical provider as some patients may be in withdrawal at their first visit. SPs will be recruited within a month of the patient’s consent.

Once enrolled in the study, patients and SPs will be interviewed separately at all time points (baseline, 3, 12 months). Participants will receive a $5 incentive for screening, $30 for the baseline interview survey, $30 for the 3-month interview and $40 for the 12-month interview. In addition, SPs assigned to INSPIRE may receive transportation and/or childcare remuneration to attend sessions as needed. All participants and SPs will be contacted for follow-up, regardless of whether they complete INSPIRE or UC, and we will conduct intent-to-treat analyses. A total of 770 dyads are expected to consent to the study, resulting in a total of 616 dyads at 3-month follow-up (assuming 80% retention) and 500 dyads at 12-month follow-up (assuming 65% retention) (see Fig. 3). To ensure robust follow-up rates, we will obtain detailed information at baseline on how to reach participants and use proven methods to minimize attrition, including an in-person baseline interview to build rapport, obtaining multiple contacts (friends/families/service providers) at baseline for individuals who would know the participants’ whereabouts, and phone/mail/text/social media reminders prior to follow-up.

**Fig. 3 Fig3:**
[figure not shown]
Study flow

We will examine patient electronic medical records (EMRs) to assess buprenorphine medication retention (i.e., no more than a 7-day lapse between prescriptions) [51, 52], healthcare utilization (e.g., number of medical and behavioral health visits), and results of urine tests (e.g., presence of buprenorphine and other opioids). All data will be stored on encrypted laptops used only for research purposes that require staff to login and provide a personal password to access. Files that have personally identified health information will also be password protected.

Randomization will conducted by research staff at the dyad-level such that patients and SPs both need to consent to be randomized. Dyads will be stratified by clinic and by SP type. We will stratify participating SPs who are patients’ parents equally to INSPIRE or UC because of existing CRAFT studies showing a stronger effect of CRAFT for parents [8] using permuted block randomization with random size blocks. This ensures the number of people allocated to each group is approximately equal throughout recruitment [53]. Data collectors will not be blind to SP intervention condition because they will need to schedule SPs for the INSPIRE class, but are independent and not part of the core research team. In addition, to minimize bias, they will emphasize to participants that their responses would be confidential and not conveyed to the clinics, will conduct follow-up interviews outside of the clinic, and will build rapport with participants to increase self-report validity.

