#### Outcomes

Our primary outcome is patient retention on buprenorphine, measured using data from the EMR, defined as buprenorphine prescriptions of at least 6 and 12 months with no more than a 7-day lapse between prescriptions (see Table 2) [8, 51, 52, 56]. We have two sets of secondary outcomes that correspond to the effectiveness of INSPIRE (specific aim 1). For the patient, we will validate adherence using urine test results in the EMR for buprenorphine metabolites, and will assess, through patient self-report, patient opioid and other substance use in the past month, overdose risk, substance use problems, health, other employment, quality of life, communication, employment, and treatment satisfaction. For the SP, our secondary outcomes are self-reported and will include the SP’s physical and mental health (depression and anxiety), substance use, quality of life, and relationship quality with their person. These outcomes have been validated with high psychometric properties in existing CRAFT trials [8, 19–24]. Self-report will be assessed via in-person interview during baseline, and phone-based interviews at 3- and 12-month follow-ups. RAND staff who conduct interviews will be masked to condition.

**Table 2 Tab2:** Outcome measures

Source	Timepoint	Outcome	Description
Primary outcome measures			
EMR	6, 12	Buprenorphine retention	Percentage of patients who initiated buprenorphine who have at least 6 and 12 months of continuous treatment with buprenorphine with no more than a 7-day lapse between prescriptions [51, 52] Number of days of longest continuous buprenorphine treatment with no breaks in care

Source		Outcome	Description
Secondary patient outcome measures			
P INT SP INT	BL, 3, 12 BL, 3, 12	Patient opioid use	Heroin, prescription opioid, and other opioid use in the past 30 days using questions from the National Survey on Drug Use and Health [57–59]
EMR	6, 12	Medication adherence	Percentage of patients with a buprenorphine prescription with a urine test positive for buprenorphine metabolites
EMR	6, 12	OUD treatment retention	Percentage of patients who initiated OBOT who had continued visits (no more than a 30-day lapse between visits) with any provider for a substance use disorder for 3, 6, and 12 months [8, 56]
P INT SP INT	BL, 3, 12 BL, 3, 12	Patient other substance use	Alcohol and other drug use in the past 30 days [58, 59]
P INT	BL, 3, 12	Overdose risk	Opioid Overdose Risk Assessment scale [60]

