P INT	BL, 3, 12	Patient Substance use problems	Substance-related problems in the past 30 days using the Short Inventory of Problems
P INT	BL, 3, 12	Patient health	Physical health in the past 30 days; depression and anxiety
P INT	BL, 3, 12	Quality of life	Functional impairment in work/school, family, and social life using the 5-item Sheehan Disability Scale [61]
P INT	BL, 3, 12	Communication	Adapted from the FACES IV [62]
P INT	BL, 3, 12	Employment status	Full-time, part-time, unemployed, other (e.g., students, persons keeping house or caring for children full time, retired or disabled persons) [63]
EMR P INT	6, 12 BL, 3, 12	Healthcare utilization	Number of outpatient medical and behavioral health visits over the 12-month period
P INT	3, 12	Treatment satisfaction	Client Satisfaction Questionnaire (CSQ-8) [64]
Secondary SP outcome measures			
SP INT	BL, 3, 12	Health	Physical health in the past 30 days; depression and anxiety
SP INT	BL, 3, 12	Substance use	Alcohol and other drug use in the past 30 days [58, 59]
SP INT	BL, 3, 12	Quality of life	Functional impairment in work/school, family, and social life using the 5-item Sheehan Disability Scale [61]
SP INT	BL, 3, 12	Communication	Adapted from the FACES IV [62]
SP INT	3	INSPIRE satisfaction	Client Satisfaction Questionnaire (CSQ-8) adapted to INSPIRE [64]

BL: baseline; 3: 3-month follow-up; 6: 6-month; 12: 12-month follow-up; EMR: electronic medical record; P INT: patient interview; SP INT: support person interview; FACES IV: Family Adaptability and Cohesion Scale IV; OBOT: office-based opioid treatment

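### The protocol says both that the follow-up interviewers know the arm and that interviewers are masked; the two statements must be reconciled for the interview-based secondary outcomes

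*Protocol article*

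**What the plan says.** The randomization paragraph of the Phase 3 section, after Figure 3, is open about blinding: "Data collectors will not be blind to SP intervention condition because they will need to schedule SPs for the INSPIRE class". It adds that these staff are independent of the core research team. To limit bias, it says, they will stress that answers are confidential and not passed to the clinics, will build rapport, and "will conduct follow-up interviews outside of the clinic".

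The Outcomes section covers the same interviews: "Self-report will be assessed via in-person interview during baseline, and phone-based interviews at 3- and 12-month follow-ups". The next sentence reads: "RAND staff who conduct interviews will be masked to condition".

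That section also shows how much depends on the interviews. On SPs it says: "For the SP, our secondary outcomes are self-reported". Patient outcomes to be assessed include, "through patient self-report, patient opioid and other substance use in the past month, overdose risk, substance use problems, health", and several more. The primary outcome, buprenorphine retention, comes from the EMR. Table 2 also lists, in the 3-month SP interview only, satisfaction measured by the "Client Satisfaction Questionnaire (CSQ-8) adapted to INSPIRE".

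**The concern.** One section claims a safeguard that another section denies. Masked assessment is a standard item when readers judge risk of bias in self-reported outcomes. It matters more here because SPs necessarily know whether they were offered the groups, so the interviewer is the only party to the interview who could be kept unaware. A results paper that followed the Outcomes section would claim masked interviews, while one that followed the Phase 3 section would report open ones. Readers would weigh the same secondary findings differently. The hypothesis under Specific aims and hypotheses that SPs will have better health and quality of life rests entirely on these interviews.

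**Working it through.** The plan gives no figure on this point, so the check is a comparison of texts and a count of the outcomes affected.

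**1. Who conducts the follow-up interviews?**
- Phase 3: the data collectors know the condition. The sentence on limiting bias carries on with the same subject and assigns them the follow-up interviews.
- Outcomes: the staff who conduct interviews are masked.

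Both statements therefore describe the people taking the follow-up interviews, and they give opposite blinding status.

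**2. Can the two be read together?**
- *Two teams.* The labels differ (data collectors, RAND staff), but no section describes a second team. The Phase 3 text itself gives follow-up interviewing to the staff who are not blind.
- *Masking at baseline only.* The masking sentence directly follows one that names baseline, 3 months and 12 months, and it sets no limit on time point.
- *Masking for patient interviews only.* The Phase 3 section says patients and SPs are interviewed separately, but neither blinding statement distinguishes between them.
- *Off-site versus telephone.* Interviews outside the clinic and interviews by telephone are compatible, so no contradiction arises there.

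**3. What is affected?** Secondary outcomes in Table 2, by source:

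| | Interview only | EMR and interview | EMR only | Total |
|---|---|---|---|---|
| Patient | 9 | 1 (healthcare utilization) | 2 (medication adherence, OUD treatment retention) | 12 |
| SP | 5 | 0 | 0 | 5 |
| Total | 14 | 1 | 2 | 17 |

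The INSPIRE satisfaction scale is one of the five SP outcomes. It is specific to the intervention, so it offers no between-arm contrast to bias. That leaves 14 − 1 = 13 interview-only outcomes with a comparison of arms, plus the interview part of healthcare utilization.

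**4. What is not affected?** Retention is measured from EMR prescriptions. The sample size section uses 51% versus 65% retained, 250 dyads per arm and alpha of 0.05/2. None of these depends on who is masked.

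**5. Can the interview itself reveal the arm?** At 3 months the SP interview contains satisfaction items adapted to INSPIRE. Put to an INSPIRE SP, they disclose the condition to an interviewer who was unaware until then. This can happen only in that interview, since patients are interviewed separately and the scale is not repeated at 12 months.

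**The case against.** The strongest reply is that the Phase 3 section makes a deliberate and reasoned choice. It says plainly that data collectors are not blind, explains why, and offers safeguards: independence from the core team, confidentiality, no reporting back to clinics, and interviews held elsewhere. On that view the plan is sound and one sentence in the Outcomes section is a slip. The primary outcome and its power are unaffected in any case.

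Much of this stands. Using unmasked collectors is not itself an error, and the safeguards deserve credit. They do not remove the contradiction, because none of them keeps the interviewer from knowing the arm.

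Three stronger readings are tempting, and the documents support none of them:
- *That the masking claim is the false one.* The detail in the Phase 3 text makes this the likelier reading, but the article does not settle it. A separate masked team may exist and simply not be described, in which case the Phase 3 text needs the correction.
- *That the interview results will be biased by some stated amount.* The article gives no planned effect for any interview outcome and no information on how far reporting shifts when interviewers know the arm. The planned 14-point difference (65 − 51) belongs to EMR retention and is no yardstick for these outcomes.
- *That SPs trained in INSPIRE will report patient opioid use differently.* This is conjecture about respondents, who know what they attended whoever interviews them. It is separate from the masking of interviewers.

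**Conclusion.** The point holds as an internal inconsistency of moderate severity. The article assigns the follow-up interviews to staff who know the condition and also says that interviewers are masked. One statement has to change. The reach is the between-arm comparisons of interviewer-collected secondary outcomes at 3 and 12 months: 13 interview-only outcomes and part of a fourteenth. The EMR primary outcome, the EMR-only secondary outcomes and the power calculation are outside it.

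The conclusion rests on two readings: that the pronoun in the Phase 3 sentence refers to the data collectors, which the grammar requires, and that the masking sentence covers follow-up, which its position after the three named time points implies. No size of bias is claimed.

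**What to change.** Reconcile the two sections in one of two ways.

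1. **Describe the interviews as open.** Delete the masking sentence from the Outcomes section, keep the Phase 3 description with its safeguards, and report the interview outcomes as assessed unmasked. This is a text change only. The cost is a less favourable description of assessment.

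2. **Make the masking real.** Amend the Phase 3 text so that whoever schedules a dyad for INSPIRE does not interview that dyad. In the 3-month SP interview, ask the INSPIRE-specific satisfaction items last, so that they cannot reveal the arm before the other outcomes are recorded. If the questions to usual-care SPs about services received are asked only of that arm and in the same interview, they need the same placement; the article does not say how they are collected. The cost is scheduling discipline. The article gives no staffing figures, so whether present staff can cover it is for the study team to confirm. This option masks the interviewer only: SPs still know their own condition and may mention it.

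Neither option changes the sample size, the primary analysis or the data collected.

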#### Usual care

All patients will be receiving buprenorphine as part of usual procedures in the clinic. Services available for SPs vary by clinic and may include individual behavioral health counseling, psychoeducation groups, and standard primary care services. We will collect information from support persons in UC about the services they received to further quantify this condition.

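### The protocol says both that the follow-up interviewers know the support person's arm and that they are masked to it; the two statements need to be reconciled

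*Protocol article*

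**What the plan says.** Two places in the protocol article describe whether the people who collect outcome data know the allocation.

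- **Phase 3, paragraph on randomization (after Fig. 3):** "Data collectors will not be blind to SP intervention condition because they will need to schedule SPs for the INSPIRE class". The sentence adds a mitigation: "but are independent and not part of the core research team". The next sentence keeps the same subject and says that, to limit bias, these collectors will stress confidentiality and "will conduct follow-up interviews outside of the clinic, and will build rapport with participants to increase self-report validity".
- **Outcomes:** "Self-report will be assessed via in-person interview during baseline, and phone-based interviews at 3- and 12-month follow-ups". The sentence directly after it is "RAND staff who conduct interviews will be masked to condition".

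Two further statements bear on whether masking could be kept during an interview. Table 2 lists, for the SP interview at 3 months only, a "Client Satisfaction Questionnaire (CSQ-8) adapted to INSPIRE". The Usual care (UC) section says: "We will collect information from support persons in UC about the services they received".

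**The concern.** SPs know whether they were offered the groups, so for self-reported outcomes the interviewer is the level at which masking can be protected. The protocol claims that protection in one section and gives it up in another.

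The outcomes that rest on these interviews include patient opioid and other substance use, overdose risk, health, functioning and communication. All SP outcomes rest on them as well. The second half of the study hypothesis, that SPs will have better health and quality of life, therefore depends entirely on interview data. A reader judging risk of bias for those results would rely on the masking statement, and as the text stands it cannot be relied on.

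**Working it through.** **1. Can the two statements be read together?**

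| Question | Phase 3, randomization paragraph | Outcomes |
|---|---|---|
| Who? | Data collectors | RAND staff who interview |
| Do they conduct follow-up interviews? | Yes: "will conduct follow-up interviews outside of the clinic" | Yes, by phone at 3 and 12 months |
| Do they know the arm? | Yes, because they book SPs into INSPIRE | No |
| Limited to a time point or subgroup? | No | No |

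Separating unmasked schedulers from masked interviewers does not work, because the Phase 3 text has the unmasked collectors doing the follow-up interviews. Limiting the masking to baseline does not work either, because the masking sentence directly follows one that covers baseline and both follow-ups.

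**2. How many outcomes depend on the answer?** Count of secondary rows in Table 2 by source:

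| | Interview only | EMR and interview | EMR only | Total |
|---|---|---|---|---|
| Patient | 9 | 1 (healthcare utilization) | 2 (medication adherence by urine test; OUD treatment retention) | 12 |
| SP | 5 | 0 | 0 | 5 |
| All | 14 | 1 | 2 | 17 |

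Rows using an interview: 14 + 1 = 15 of 17. INSPIRE satisfaction applies to one arm only, so it offers no between-arm comparison to bias. Removing it leaves 15 − 1 = 14 of 17 − 1 = 16 comparable outcomes, of which 13 are interview-only and 1 is mixed.

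**3. How many interviews?** Phase 3 expects 616 dyads at 3 months and 500 at 12 months, with patient and SP interviewed separately. That gives 2 × (616 + 500) = 2,232 follow-up interviews, if both members of each dyad complete.

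**4. What could a bias do?** The documents give no estimate, so this is illustration only. Assume that true past-30-day use is 30% in both arms, that there are 250 patients per arm, and that interviewer influence lowers the INSPIRE figure by 3, 5 or 7 points. The chance of nominal significance favouring INSPIRE (two-sided 0.05) is about Φ(δ/SE − 1.96), with SE = √[0.30 × 0.70/250 + p(1 − p)/250].

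| Recorded INSPIRE rate p | δ | SE | δ/SE − 1.96 | Chance |
|---|---|---|---|---|
| 0.30 | 0 | 0.0410 | −1.96 | 2.5% |
| 0.27 | 0.03 | 0.0404 | −1.22 | 11% |
| 0.25 | 0.05 | 0.0399 | −0.71 | 24% |
| 0.23 | 0.07 | 0.0394 | −0.18 | 43% |

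A shift in the other direction would work against INSPIRE. This is an unadjusted test. The planned analysis uses mixed models with baseline covariates and reports false discovery rates for secondary analyses, so the figures show only that modest shifts could matter.

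**The case against.** The strongest reply is that data collectors and RAND interviewing staff may be different people, in which case the Outcomes section is right, the Phase 3 wording is a slip, and there is no interviewer bias. The article does not say this and describes both as interviewing, so the conflict stands. The reply does, however, block a stronger conclusion.

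A reader might infer that the interviewers will in fact be unmasked and that the secondary results will therefore favour INSPIRE. The documents do not support that. They do not settle which statement is practice, and they give neither direction nor size for any bias. Several measures are standard self-report questionnaires or survey items and not rater judgements, which limits interviewer influence without removing it. The collectors' stated independence from the core team is relevant to expectation effects. It lowers the risk, as confidentiality and rapport may, but none of these keeps the allocation from the interviewer.

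A reader might also infer that the interview content would unmask every interviewer anyway. That goes too far. The INSPIRE satisfaction scale is asked of SPs only, at 3 months only, and patients are interviewed separately. The Usual care section does not say when or how service use is collected, or that INSPIRE SPs are not asked about it. Question order is not given. These items can reveal the arm in an SP interview, but they need not affect answers already recorded.

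It is also fair to say that power, alpha and the main conclusion all rest on EMR retention, which interviewers do not touch.

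**Conclusion.** The contradiction is real, and nothing in the article resolves it. The primary outcome and the two EMR-only secondary outcomes are unaffected. If the Phase 3 statement describes practice, 14 of 16 comparable secondary outcomes (healthcare utilization only partly) are open to interviewer bias of unknown direction and size, and a report of masked assessment would be untrue. If the Outcomes statement describes practice, the Phase 3 text is wrong and only the wording needs correcting.

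The count rests on the sources listed in Table 2 and on treating INSPIRE satisfaction as a one-arm measure. Severity is moderate: one of the two statements must be corrected, but the trial's main test does not depend on it.

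**What to change.** Reconcile the two passages. State who books SPs into INSPIRE, who conducts the 3- and 12-month interviews, and whether those interviewers know the allocation.

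- **Preferred.** Give INSPIRE booking to existing staff who do not conduct the 3- and 12-month interviews, for example the group facilitators, and keep the interviewers masked. Giving it to the research staff who randomize helps only if they are not also the interviewers, which the article does not say. In the SP interview, place the INSPIRE satisfaction scale and any service-use items after all outcome items.
- **If booking cannot be moved.** Delete the masking sentence in Outcomes and report interview-based outcomes as assessed unmasked.

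The first option costs a small reassignment of a scheduling task and a change in question order. The second costs a less favourable masking statement. Neither needs more participants.

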#### INSPIRE facilitators and training

Medical and behavioral health staff members who will be facilitating INSPIRE groups (selected nurses, case managers, peer recovery specialists, and licensed social workers) from each CHC will attend a 1-day training, conducted by the study team. The training will involve a mix of didactic presentation, demonstration, and practice sessions involving role-plays. Role-plays are central to practicing INSPIRE and are highlighted throughout the training to give facilitators the opportunity to practice and receive feedback. The training will focus on group facilitation skills, safety planning, enhancing SP motivation to engage in INSPIRE, and the importance of helping the SP to increase positive interactions between the SP and patient. Key techniques, such as communication and recognizing and reinforcing positive behaviors, will be taught. Skills also include ways to reinforce and shape patient behaviors with an emphasis on refraining from interfering in naturally occurring OUD consequences. The training will focus on ways the SPs can respond to problematic patient behaviors, as well as problem-solving and ways to facilitate patients’ retention in buprenorphine. Staff will receive weekly supervision thereafter and will be monitored using a fidelity checklist.

